#### Entomological

Based on a study using light traps in an adjacent study area in Burkina Faso in 2010, we expect that the mean number of female *An. gambiae* s.l. per trap/village will be 45 during the rainy season (with a CV = 0.35). In order to demonstrate a 33% reduction in blood-questing indoor mosquitoes (that is, unfed *An. gambiae*) associated with PPF-LLIN, with 80% power and at the 5% level of significance, would require 6 houses in each cluster and 14 clusters in each arm of the trial over 2 years [35]. To allow for loss to follow-up due to people moving house during the study period we propose to include at least 6 houses in each cluster and 20 clusters in each study arm for 2 years.

### Data handling and record keeping

The demographic data will be recorded by fieldworkers and the clinical data by study nurses on standardised data forms. Each child in the cohort will be identified by a unique identification number and non-cohort children participating in the cross-sectional surveys will be identified by their demographic surveillance number. All forms and datasets will identify participants by these numbers, and names will not be entered.

After the collection and verification, data will be moved to the data management unit in Banfora for data entry. Data forms will be double entered (firstly by field staff and then by data entry staff) and the entries combined and errors corrected to produce a single dataset. This will be checked for consistency by generic and study-specific algorithms designed to identify sources of error. Inconsistencies will be checked against the original forms and errors will be corrected where possible, for example by checking in the field, or put to missing, to produce final datasets.

All forms with subject names and/or clinical data will be kept in a cabinet and locked when not in use; the key will be kept by the study coordinator or delegate. The electronic datasets will be password protected. Hard copies of the data will be stored for 10 years. Clinical forms will be kept separately from that containing personal identification (for example, consent forms). The datasets will be password protected and only accessed by authorized study staff and the study data manager until after publication. Data will be stored for at least 10 years.

### Analytical plan

A per protocol and an intention to treat analysis will be conducted.

### Outcome 1 – malaria morbidity

The primary endpoint is a comparison of the incidence of clinical episodes of malaria in children in the 2 intervention groups, measured by PCD. After a case of malaria is treated, time of observation will be censored for 3 weeks and further attacks of malaria during this period are not considered. History of travel away from the village for periods of over a week will be captured by the monthly surveys and time at risk will be censored for such periods. In addition, malaria cases in children who resided outside their study village for more than half the elapsed study period at the time of illness will be censored. An initial analysis will compare the incidence rates between the 2 intervention groups, adjusted for duration of sleeping under a PPF-LLIN. However, the main endpoint analysis will also adjust for distance between village clusters with different types of nets [38]. This adjustment is critical since the impact of PPF-LLIN is likely to increase as they cover larger areas and so reduce the spill over of mosquitoes from villages with LLINs. Specifically, a village with PPF-LLIN surrounded by other villages with PPF-LLIN is likely to be better protected against malaria than a village with PPF-LLIN surrounded by villages with LLINs. Since the replacement of drop-out individuals may introduce bias we will repeat the primary analysis including and excluding this group.

Each of the outcome measures collected in this study will be analysed using multi-level statistical modelling methods, with appropriate distributional assumptions (for example, logistic, Poisson or negative binomial for counts and rates, normal for biochemical measures, and so forth). Within each model, effect size (that is, difference between PPF-LLIN and LLIN clusters) will, as appropriate, be adjusted for clustering within the groups of villages, the shortest distance between each PPF-LLIN cluster of villages and its nearest control, LLIN, village-cluster, the time of use of current nets (to account for different times in PPF-LLIN and LLIN conditions for each group of villages), village-cluster size, sex distribution, house design, bed net use, and other relevant potential confounding factors. Effect sizes will be presented as mean differences or rate differences/ratios as appropriate, with 95% confidence intervals.

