**Figure 1 Fig1:**
[figure not shown]
**Step-wedge design for roll-out of bednets.** Permethrin-treated nets were given to all clusters in May 2014, followed by pyriproxyfen & permethrin treated nets (red) being rolled-out to different clusters in 2014 and 2015.

Clinical malaria will be recorded by study nurses using PCD methods during the rainy seasons in years 1 and 2. Parasites will be detected by rapid diagnostic tests (RDTs) and thick smears will be stained for confirmation and parasite counting by study staff. Treatment will follow government guidelines.

The study cohort will be surveyed for malaria indices (parasite prevalence, anaemia and spleen rate) at the beginning and end of both transmission seasons to generate data for the secondary endpoints. Where possible, at each malaria survey except the first, an average of 50 children from each village cluster who have not been enrolled in the cohort but are of a similar age will also be surveyed for these malaria indices. This additional group of children may better reflect the *Plasmodium falciparum* parasite rate in the population than children in the PCD cohort. Baseline data from the cohort will be used to compare the village clusters before the interventions, and the cohort from each village cluster provides its own baseline data before net exchange to PPF-LLIN. In addition, we will request anonymized medical records from the 6 health facilities located in the valley and use these to document clinical malaria in children aged 6 months to 5 years living in villages outside the study area. These children represent a further control group which can be used to track temporal changes in malaria incidence during the study period. If malaria declines in the study area in year 2, but not outside, we can be confident that the decline is due to the intervention, rather than confounding factors such as low rainfall. The end-of-season survey data will also be used to attempt to define a *P. falciparum* parasitaemia cut-off giving optimum sensitivity and specificity for malaria cases in this setting [21].

A schematic representation of the trial is shown in Figure 2.

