### Interventions

#### Long-lasting insecticidal nets

The LLINs are manufactured by Sumitomo Chemical (Japan). These are WHO recommended and meet WHO specifications with 2% w/w permethrin incorporated into polyethylene fibres giving adequate release of permethrin for about 5 years. These nets will be distributed at the beginning of the main transmission season, at no cost to the recipients. We will use white ‘extra family’ size rectangular nets (180 cm wide × 190 cm long × 150 cm high) of a white colour throughout. Government Roll Back Malaria information, education and communication procedures will be followed to encourage correct net use and maintenance, including supplying the nets in individual pre-opened bags.

LLINs will be stored locked at ambient temperature in Banfora, under the control of a delegated individual, ready to be moved to the Health Facilities in batches by lorries and held by the officers in charge before being transported to the villages for distribution by the study team. In advance of distribution, the number of beds/sleeping places and the number with LLINs will be counted. New nets will be exchanged for old nets at the household level to achieve one LLIN per bed/sleeping place. Net use by study children will be monitored during the monthly travel/residence surveys during the 2014 and 2015 transmission seasons.

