### Study procedures and evaluations

LLIN distribution will be completed in mid-2014. Study nurses and field assistants will be provided with refresher training on diagnosis of malaria, the use of RDT and study procedures in 2014 and 2015 before the transmission season.

The compound of each study child will be geo-referenced using a hand-held global positioning system, as the primary data analysis has a spatial component. Travel/residence of cohort children will be assessed at monthly intervals on brief questionnaires to estimate their time at risk, and their bed net usage will be assessed at the same time.

Thick blood films will be stained with Giemsa and examined under 1000-fold magnification by trained, experienced microscopists. Parasite counts will be recorded per high power field and 100 fields will be counted before a slide is declared negative. Parasite density will be estimated assuming that one parasite per high power field equals 500 parasites/μL [34]. 2 slides will be prepared from each subject and read separately by 2 experienced microscopists; discrepancies in positive and negative reads and those greater than 10-fold between the 2 reads will be resolved by the microscopy supervisor. Field staff will deliver all CRF to the study physician within 2 days of the clinical attack or survey date. The study physician will check all CRFs weekly for completion and data consistency.

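### The residence rule in the primary analysis removes malaria cases but not the matching person-time, so incidence is understated, possibly unequally between the two nets

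*Protocol article*

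**What the plan says.** The Outcome 1 section of the Protocol article gives three exclusions in a row.

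1. After a treated case, "time of observation will be censored for 3 weeks and further attacks of malaria during this period are not considered". This acts on time and cases together.
2. For travel of over a week, "time at risk will be censored for such periods". This acts on time.
3. In addition, the plan censors "malaria cases in children who resided outside their study village for more than half the elapsed study period at the time of illness". This acts on cases, and nothing is said about time.

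Study procedures and evaluations gives the purpose of the travel data: "Travel/residence of cohort children will be assessed at monthly intervals on brief questionnaires to estimate their time at risk".

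The start of the elapsed study period is not defined. It could be the first net distribution ("Permethrin-treated nets were given to all clusters in May 2014", Figure 1), the start of passive case detection in June 2014, or the child's own enrolment. The last would differ for replacement children, who enter in May 2015.

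**The concern.** An incidence rate needs numerator and denominator to be cut by the same rule. The third exclusion takes effect only when a child falls ill. A child who has been away for more than half the elapsed time and is now home keeps adding person-days, yet any case on those days is discarded. An equally mobile child who stays well adds the same days and is never examined under the rule. The rate is therefore too low.

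Excluding infections that may have been acquired elsewhere is a reasonable aim. But once such days cannot yield a countable case, they are not time at risk.

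The between-net comparison is exposed because the threshold moves with elapsed time and the nets are rolled out over calendar time. Any imbalance in deletions then enters the rate ratio for the primary endpoint.

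**Working it through.** **Plan's own figure.** The plan attaches no number to this rule. The nearest figure is the 19.38 clusters per arm in the sample size rationale. The inputs given there are rates of 1.5 and 1.125, CV 0.25, 90% power and 5% significance (two-sided assumed). Fifty children over 2 seasons are taken as 100 child-years per cluster. Then

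c = 1 + (1.960 + 1.282)² × [(1.5 + 1.125)/100 + 0.25² × (1.5² + 1.125²)] / 0.375² = 19.38.

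The figure is reproduced. No residence term enters it, so this point does not change it.

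**Mismatch for one child.** Suppose a child is away for the first d days and home afterwards. The fraction away on day t is d/t, which exceeds one half until day 2d − 1. That leaves d − 1 days at home on which a case would be dropped. For d = 20, 20/39 = 0.513 and 20/40 = 0.500, so days 21 to 39 are affected: 19 child-days. Days 1 to 20 leave the denominator under the travel rule, but days 21 to 39 do not.

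**Threshold, counting from 1 June 2014.** A case is dropped if the child was away more than 15 days by day 30, more than 107 by day 214 (end of December 2014), or more than 182 by day 365. The same trip can delete a case in one month and not in another.

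**Link to net type.** The Design section has 5 of 40 clusters switching each month from June to September in both years. Surveillance covers June to December in both years, which is 14 × 40 = 560 cluster-months.

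- Exchange at the start of the month: LLIN time is (35 + 30 + 25 + 20 + 3 × 20) + (15 + 10 + 5) = 200, and PPF-LLIN time is 360. June–July 2014 is 65/200 = 32.5% of LLIN time and 15/360 = 4.2% of PPF-LLIN time.
- Exchange at the end of the month: the totals are 240 and 320, and the shares are 75/240 = 31.3% and 5/320 = 1.6%.

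The Randomisation section instead has half the clusters converted by the end of July 2014, so these shares depend on which passage is followed.

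**Size under assumed travel.** Let q be the share of in-village person-time on which a case would be dropped. The unadjusted rate ratio is multiplied by (1 − q for PPF-LLIN)/(1 − q for LLIN). A day-level simulation used 20,000 children per scenario. It varied the origin (May or June 2014), the exchange timing (start or end of month) and the seasonal shape of cases (flat or peaked). The trip patterns are assumptions; the documents give none.

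| Mean trip, trips per year | LLIN cases dropped | PPF-LLIN cases dropped | Share of drops in June–Sept 2014 | Factor on rate ratio |
|---|---|---|---|---|
| 14 days, 1–2 | 0.2–0.6% | under 0.2% | 85–93% | 1.002–1.004 |
| 30 days, 2 | 1.8–2.3% | 0.9–1.2% | 42–61% | 1.007–1.013 |
| 60 days, 1 | 1.7–2.2% | 1.9% | 19–33% | 0.998–1.003 |
| 120 days, 1 | 2.5–3.3% | 5.6–5.9% | 6–14% | 0.968–0.975 |
| 60 days, 3 | 6.6–8.3% | 9.6–10.2% | 13–25% | 0.965–0.981 |

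A true ratio of 0.75 would appear as about 0.724 to 0.760. If the matching person-time is removed with the cases, the factor is 1.000.

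**The case against.** The article does not say that this person-time is kept. It uses the verb it applies to time in the two preceding rules, and the travel data are collected to estimate time at risk, so the authors may have meant both. Implementation could also be left to an analysis plan that is not shown. Part of this stands: the intent may be sound. But the text says what happens to time under the other two rules and names only cases here. An analyst following it would compute the wrong rate.

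It also stands that the effect is limited. Absences of over a week are already removed. Carers are asked for assurance that the child will stay in the village during the transmission season. Any between-net bias works through calendar time, so period adjustment would reduce it. The adjusters listed include time of use of current nets and other relevant confounders, but calendar period is not named.

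Three stronger readings are tempting and are not supported.

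- **Most deletions fall early, under LLIN, and bias the trial against PPF-LLIN.** The low early threshold suggests this, but it holds only for short trips, where the factor is at most 1.004. With long absences most drops come later and the bias favours PPF-LLIN.
- **A distortion of about 9%.** If 10% of home time were affected early and 2% late, 0.98/0.90 = 1.09. That treats all LLIN time as early and all PPF-LLIN time as late. With the start-of-month shares above, LLIN loses 0.325 × 10% + 0.675 × 2% = 4.6% and PPF-LLIN 0.042 × 10% + 0.958 × 2% = 2.3%. The ratio is 0.977/0.954 = 1.02, and the 10% and 2% are themselves assumptions.
- **No residence data exist for January–May 2015.** The interventions section monitors net use "during the monthly travel/residence surveys during the 2014 and 2015 transmission seasons", but the procedures section says only monthly, and a monthly demographic surveillance system is described. A gap is an inference, and whether the dry season counts as elapsed time is undefined.

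**Conclusion.** The point holds in a narrow form. As written, the residence rule removes cases without the matching in-village person-time, so incidence is understated whenever any child passes the threshold. Because the threshold depends on elapsed time and net type on calendar time, the deletion can differ between nets. The direction is unknown. The factor on the rate ratio is roughly 0.97 to 1.01 before period adjustment, and under 0.5% from unity if trips are short. These sizes rest entirely on assumed travel and on the roll-out in the Design section. Part of the range exaggerates the benefit of PPF-LLIN, so the rule cannot be defended as merely conservative. Severity is minor to moderate: it is a misspecified primary-endpoint rule with a small likely effect and no effect on sample size.

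**What to change.** Define residence eligibility for every child-day from the travel record, whether or not the child is ill. State the origin of the elapsed study period, including for replacement children, and whether January to May 2015 counts. On days when a child fails the criterion, remove both the person-time and any case arising in it. Alternatively, drop the rule and rely on the existing removal of absences of over a week.

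Either change is about a sentence in the analysis plan and uses travel data already being collected. The first costs a small amount of person-time. The second costs none but keeps cases in recently returned children, some of which may have been acquired elsewhere.

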## Methods/Design

### Study area and participant eligibility

The study site is situated south of the road from Banfora and Sideradougou (10° 56’ 00” N, 004° 46’ 00” W) and is approximately 1,250 km^2^, bisected by a river in a north-south axis. It is an area of West Sudanian savannah and the climate consists of a rainy season from May to October with little rain in other months. This defines the seasonal malaria transmission with most malaria episodes experienced during or immediately following the rainy season. The study area has 6 health centres and every village is affiliated to only 1 health centre. A baseline demographic survey conducted in July 2013 enumerated 63,903 individuals living in 93 villages, with most people living in small rural villages in houses made with mud or cement walls and thatched or metal roofs. The study’s field station is based at Banfora town which is the main town in the district. This study is in an area of cotton growing since 1968 with both the S and M forms of *An. gambiae* s.s. [20].

Each village or groups of neighbouring villages with more than 50 children aged 6 months to 5 years old will be invited to join the study, and will constitute a single cluster. Following local custom, sensitisation will start by discussions with community elders and then with representatives of the whole study community in order to explain the nature and requirements of the study. Village level permission will then be sought after sensitization meetings attended by village community leaders and health staff at the health centres; attendees’ names and village of residence will be documented. Witnessed written consent will also be sought from each net recipient, before net donation and exchange (Additional file 1). During these procedures it will be made clear that people will be able to leave the study at any time but that their original net will not be returned.

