### Design

A cluster-randomised controlled trial design will be used since: i) LLINs are a community-level intervention; and ii) the village cluster is a suitable unit for randomization since they represent a discrete spatial cluster. At the outset of the study, all households will be provided with new LLINs at the rate of 1.1 nets for every 2 people in their household; this will approximate 1 for every sleeping place. Each month for the next 4 months after LLIN donation, residents in 5 randomly selected village clusters will be asked to exchange their LLINs for PPF-LLIN. Stratified, random sampling will be used to ensure that by the end of year 1 (September 2014) there will be a similar number of residents with and without PPF-LLINs affiliated to each health centre. Every month from June to September in 2015, an additional 5 village clusters will be provided with PPF-LLIN, thus by the end of September 2015 all clusters will have PPF-LLIN (Figure 1). It is important that within the study area there are no villages that are not enrolled in the study in order for the PPF-LLIN to have maximum impact on larval populations and minimize the spill-over of mosquitoes from villages without these nets. LLINs and PPF-LLIN will be the same shape, size and colour and marked with a unique code number, so that the investigators are blinded to the identity of the net (apart from those field assistants distributing nets).

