### Sample size rationale

#### Clinical

LLINs reduce malaria morbidity by approximately 50% [3]. The combined impact of using permethrin, a pyrethroid, and pyriproxyfen is unknown. If the effects were simply additive a mean reduction of 75% could be anticipated for PPF-LLIN (that is, LLINs alone will reduce incidence by 50%, and if we assume the pyriproxyfen alone may reduce the remaining 50% incidence by half, there would be a 75% reduction). However, the effects may be synergistic (for example, by having a mass killing effect). In order to change national guidelines on the use of LLINs we consider that PPF-LLIN should be at least 25% more effective than LLINs. A study of 3- to 60-month old children in Burkina Faso reported an incidence of clinical episodes of malaria of 1.5 episodes/child/year. Malaria incidence data for 2012 from villages in the Banfora region of Burkina Faso indicate the coefficient of variation (CV) for this study will be approximately 0.25. Regarding this study as a simple cluster-randomised controlled trial, assuming CV = 0.25 and that an average of 50 children will be monitored in each cluster for 2 seasons, the study will have 90% power to detect a 25% increase in protection with PPF-LLIN compared to LLINs (that is, a reduction in the incidence of clinical episodes of malaria from 1.5 to 1.125 episodes/child/year) at the 5% level of significance if there are 19.38 clusters in each arm [35]; we thus propose to recruit 20 village clusters into each arm of the study. Adjusting for a coefficient of up to 0.5 for the differences in cluster size (the data from Banfora cited above suggest that this CV will be much lower - approximately 15%), 20 clusters per study arm will still provide the study with 85% power [36].

Assuming prevalence of *P. falciparum* around 30% [37], 20 clusters in each arm and CV = 0.3, the study could detect a 30% reduction of prevalence, with 5% significance and 80% power, between the study arms if longitudinal cohorts for each cluster contain at least 45 children. Assuming mean Hb around 10.5g/dL, 20 clusters in each arm and CV = 0.1, the study could detect a difference of 1.0g/dL in mean Hb, with 5% significance and 80% power, between the study arms if at least 35 children were followed in each cluster .

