### Outcome 2 - malaria transmission

Differences in malaria transmission experienced in the 2 arms of the study will be estimated by comparing the EIR in village clusters between the 2 arms, adjusted for length of time under PPF-LLIN and distance between village clusters with the 2 different types of nets. Generalised estimating equations will be used to estimate differences in numbers of indoor mosquitoes, adjusting for repeated measures within clusters and possible covariates.

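### The roll-out ties net type to season and year, but the only time adjustments the plan names are net duration and net age; calendar month should be a mandatory model term

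*Protocol article*

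**What the plan says.** All clusters receive LLINs in May 2014. Under Design, five clusters a month then exchange them for PPF-LLIN over four months of 2014, and "Every month from June to September in 2015, an additional 5 village clusters will be provided with PPF-LLIN". Passive case detection covers June to December of both years (Clinical data collection and patient treatments). On the climate, the section on study area and eligibility states: "This defines the seasonal malaria transmission with most malaria episodes experienced during or immediately following the rainy season".

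Under Outcome 1 – malaria morbidity, an initial analysis adjusts for duration of sleeping under a PPF-LLIN, and the main analysis adds distance between clusters with different nets. The model list then names, among other covariates, "the time of use of current nets (to account for different times in PPF-LLIN and LLIN conditions for each group of villages". The list applies where appropriate and ends by admitting other relevant confounders. Under Outcome 2 – malaria transmission, EIR is "adjusted for length of time under PPF-LLIN and distance between village clusters with the 2 different types of nets"; mosquito numbers are modelled with possible covariates. The secondary endpoints use unpaired tests and regressions with individual-level covariates. Month, season and year are not named in any of these sections.

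Secular change is addressed elsewhere. Design plans to use health-facility records of children living outside the study area, and concludes that if malaria falls inside but not outside, "we can be confident that the decline is due to the intervention". The Discussion says that the place and timing of cases will be considered.

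**The concern.** In a one-way roll-out, unexchanged time is early time. Here that means early in the season and mostly in the first year, while exchanged time is late in the season and mostly in the second year. Unless the model separates calendar time from net type, a seasonal peak or a good or bad malaria year is partly read as a net effect.

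The plan does more than leave a detail open: it names a time covariate and gives it the task of accounting for differing times in the two conditions. That covariate restarts at each exchange. It tracks the calendar only while a cluster is still on LLINs, so it cannot do the job. At stake are the primary rate ratio and the EIR comparison: a real 25% reduction could be hidden, or one could appear where there is none.

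**Working it through.** **1. The plan's own figure.** Inputs from the sample size section: "the study will have 90% power to detect a 25% increase in protection", "a reduction in the incidence of clinical episodes of malaria from 1.5 to 1.125 episodes/child/year", CV 0.25, and 50 children for 2 seasons, taken as y = 100 child-years per cluster. The standard formula for rates in a parallel cluster trial, two-sided 5%, is

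c = 1 + (1.960 + 1.282)² × [(λ0 + λ1)/y + CV²(λ0² + λ1²)] / (λ0 − λ1)²

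= 1 + 10.507 × [2.625/100 + 0.0625 × (2.25 + 1.2656)] / 0.1406 = 19.38.

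This matches the stated 19.38. The figure is right for the parallel design it assumes; that design has no calendar periods.

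**2. Net type by month.** With 40 clusters and five exchanges a month as given in Design, counting an exchange at once, the clusters still on LLIN are:

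| | Jun | Jul | Aug | Sep | Oct | Nov | Dec | Sum |
|---|---|---|---|---|---|---|---|---|
| 2014 | 35 | 30 | 25 | 20 | 20 | 20 | 20 | 170 |
| 2015 | 15 | 10 | 5 | 0 | 0 | 0 | 0 | 30 |

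LLIN cluster-months: 200, of which 170 (85%) are in 2014. PPF-LLIN cluster-months: 560 − 200 = 360, of which 280 − 30 = 250 (69%) are in 2015. From September 2015 (October if exchange takes a month to count) there is no LLIN comparator.

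**3. A crude check by hand.** The documents give no monthly curve, so this one is assumed: June to December shares of 5, 10, 18, 23, 22, 14 and 8%, equal years, no true net effect.
- LLIN, 2014: 35×5 + 30×10 + 25×18 + 20×67 = 2,265. LLIN, 2015: 15×5 + 10×10 + 5×18 = 265. Mean: 2,530/200 = 12.65.
- PPF-LLIN: 8,000 − 2,530 = 5,470. Mean: 5,470/360 = 15.19.
- Crude ratio: 15.19/12.65 = 1.20, although the nets do not differ.

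**4. With the named covariate.** Poisson models were fitted to expected counts (40 clusters × 14 months) with cluster effects, net type and linear age of the current net (from May 2014 for LLIN, from exchange for PPF-LLIN). The flatter assumed curve is 10, 13, 16, 18, 17, 14 and 12%. Estimates when the true ratio is 1.00:

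| Assumed season | Year 2/year 1 = 0.75 | 1.00 | 1.25 |
|---|---|---|---|
| Flat | 0.80 | 1.00 | 1.20 |
| Flatter | 0.89 | 1.11 | 1.34 |
| Peaked | 1.02 | 1.29 | 1.56 |

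With a true ratio of 0.75, the peaked season and equal years, the estimate is 0.97. A wider set (early, middle and late peaks; year ratios 0.7 to 1.3; exchange counted at once or a month later) gives 0.70 to 1.65 for a true 1.00, and 0.53 to 1.24 for a true 0.75.

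**5. With calendar-month effects.** Adding one effect per month-year returns the true ratio, 1.00 or 0.75, in every scenario.

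**6. Precision.** Generalised least squares on the log rate, with a cluster random effect of CV 0.25 and a constant net effect: the standard error rises from 0.034 to 0.048 with 100 child-years per cluster, and from 0.044 to 0.062 with 58.3 (50 × 14/12). Power is Φ(|ln 0.75|/SE − 1.96). In the least favourable case run (58.3 child-years, assumed extra cluster-by-month variance 0.06, SE 0.070), this is Φ(0.288/0.070 − 1.96), about 98.4%.

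**7. An effect shared across the area.** Suppose the total ratio at full coverage is 0.75 and half of it (log scale) reaches all clusters in proportion to coverage. Month effects absorb the shared half, and the adjusted ratio is √0.75 = 0.87. If all of it is shared, the adjusted ratio is 1.00.

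**The case against.** A reader might infer that no analysis adjusts for calendar time and that the primary ratio is badly biased. The documents do not support either statement. The covariate list is open-ended, the Discussion promises attention to when cases occur, Design plans an external comparison, and an analysis plan that is not shown may contain period terms. The size and even the sign of any bias depend on a seasonal curve and a year-to-year change that the documents do not give. In the table above, the peaked season combined with a 25% fall in year 2 leaves an estimate of only 1.02.

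Two further inferences also fail. The outside-area records cannot be dismissed as lacking study nurses or person-time: they come from 6 health facilities in the valley, study nurses are placed in 6 facilities within the study area, apparently the same ones, and the protocol does not say that denominators are absent. Nor are the secondary endpoints confounded throughout. The end-of-season survey in 2014 is a concurrent randomised contrast of 20 against 20 clusters, so the problem arises only when years are pooled.

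The most serious objection concerns the remedy. The protocol expects protection to grow with area-wide coverage, and coverage is itself a function of calendar month. Month effects therefore remove part of what the trial hopes to show. This stands, and is a reason to state what the adjusted ratio estimates. It is not a reason to omit the terms, because without them the shared benefit cannot be told apart from season and year.

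What remains is that a permitted covariate is not a required one, and that the covariate the plan does name for this purpose does not serve it.

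**Conclusion.** The point holds as a badly chosen time adjustment. The roll-out confounds net type with season and year, and duration under PPF-LLIN and age of the current net do not break the link. If calendar time is left out, a true ratio of 1.00 is estimated at about 0.80 to 1.56 under the nine assumed combinations of season and year ratio (0.70 to 1.65 in the wider set). The bias can thus be as large as or larger than the 25% target effect, in either direction. It is nil if the season is flat and the years are equal. All these sizes rest on assumed curves; the cluster-month counts rest on the Design schedule alone.

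The sentence on confidence in the outside-area comparison is too strong. In year 2 the cohort is older and 20 of the 40 clusters receive new nets, so a fall inside but not outside has other possible explanations.

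**What to change.** - In the primary incidence model and in the EIR and mosquito-count models, make fixed effects for calendar month-year mandatory (14 case-detection months for incidence), with a random cluster effect and a cluster-by-period effect.
- Include survey round in any secondary model that pools the two years.
- Keep the distance term, or a local-coverage term, in the main model.
- State that the month-adjusted ratio estimates the within-period contrast between net types and may understate the total effect where benefit is shared across the area. Use the distance or coverage term and the outside-area comparison as supporting evidence on that shared part.
- Reword the sentence in Design so that the outside-area comparison supports attribution to the intervention but does not establish it.

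The change is to the analysis text and needs no new data. It costs precision (standard error up by about 40%: 0.048/0.034 = 1.41). No extra clusters are implied, since power for a ratio of 0.75 stays above 98% under a constant effect. The narrower estimand is the other cost.
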